**Statistical methods**

All data will be entered by two members separately and analyzed after confirming that the data is completely consistent. We will use SPSS 22.0 for statistical analysis. For metric data, Shapiro-Wilk test will be used to check for normality. If it meets the normal distribution, it will be described by mean ± standard deviation; otherwise, it will be described by median (P25, P75). Pearson correlation analysis will be used to evaluate the correlation, and P<0.05 will be considered statistically significant. Metric data of different groups will be described statistically using mean, standard deviation, median, minimum value, and maximum value. Count data of different groups will be described statistically using frequency (composition ratio). We will use exact probability calculation or non-parametric test to analyze the changes before and after intervention in each group. Regarding drop-out analysis, we will describe the actual number of enrolled subjects, excluded subjects, and drop-out subjects one by one, and analyze the specific reasons for drop-out and exclusion. The balance analysis of baseline values will be compared using analysis of variance or exact probability calculation for demographic data and other baseline indicators to measure the balance of each group. We will list adverse events that occurred during the trial and describe the changes in laboratory test results before and after the trial, and the relationship with the intervention when abnormal changes occurred.

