**Objectives and Outcomes**

Aim 1: To determine the efficacy of mobile-based CBT intervention compared to conventional treatment for patients with premature ejaculation (PE).
- Hypothesis 1a: a significant difference in the mean scores of the premature ejaculation diagnostic tool (PEDT) is expected between the two groups within 8 weeks.

Aim 2: To determine whether the duration of mobile-based CBT intervention has an impact on the efficacy for patients with PE.
- Hypothesis 2a: some significant differences in the PEDT scores, intravaginal ejaculatory latency time (IELT), and the Female Sexual Distress Scale-Revised premature ejaculation version (FSDS-R-PE) scores are expected between the two groups at 4 and 8 weeks.

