**Group therapy**

Designated personnel at the trial center will input basic information of eligible patients into the randomization system according to the randomization table. A random number will then be generated. Patients who meet the inclusion criteria will undergo random allocation after obtaining signed informed consent.

Both patient groups received conventional treatments, including chemotherapy, traditional Chinese medicine, and instrument therapy, with treatment selection and plans based on the guidelines for diagnosis and treatment of premature ejaculation. To maximize the effectiveness of CBT interventions based on mobile devices in PE patients, we used remote management through social media software (WeChat) to address sensitive issues that may be difficult to reach in the population. We used the WeChat-MiniApp: "PE-CBT" developed by Hangzhou Kang Ming Information Technology Co., Ltd. to remotely manage the intervention group of patients. WeChat management mainly includes: (1) patients can achieve out-of-hospital coordination and management through WeChat and learn courses on cognitive-behavioral therapy; (2) researchers can track patient management through outpatient clinics (Fig 1). The specific course schedule is shown in the Fig 2. The entire course is divided into three stages. The stage 1 focuses on improving cognition, the stage 2 focuses on improving behavior, and the stage 3 focuses on reviewing.

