**Sample size**

This study adopted two control groups, namely, the remote management + conventional treatment group and the conventional treatment group, with a 2:1 ratio for enrollment. The primary research indicator was the PEDT score, with α=0.05 and β=0.2. Previous literature has shown that the PEDT score decreases by at least 2-3 points with psychological/behavioral therapy [20] and by at least 6-7 points with drug therapy [21, 22]. Given a maximum follow-up loss rate of 20% for each group, a target sample size of 300 patients, with 150 patients in each group, was determined.

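### The only efficacy test the protocol names is before-after within each arm, which does not test its between-group hypotheses

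*Protocol*

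**What the plan says.** Under Objectives and Outcomes, Hypothesis 1a reads that "a significant difference in the mean scores of the premature ejaculation diagnostic tool (PEDT) is expected between the two groups within 8 weeks". Hypothesis 2a adds PEDT, IELT and FSDS-R-PE, where differences in "scores are expected between the two groups at 4 and 8 weeks". Trial design describes a randomised, controlled, parallel-group study.

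Statistical methods names these inferential procedures:
- Shapiro-Wilk, for normality;
- Pearson correlation, with no variables named;
- for efficacy: "We will use exact probability calculation or non-parametric test to analyze the changes before and after intervention in each group";
- for baseline: "The balance analysis of baseline values will be compared using analysis of variance or exact probability calculation".

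Metric and count data of the groups are otherwise to be summarised descriptively. No test or model is named that compares the arms on a post-baseline outcome.

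Two other statements bear on the point. Group therapy says "Both patient groups received conventional treatments". Sample size cites literature that "the PEDT score decreases by at least 2-3 points with psychological/behavioral therapy" and "by at least 6-7 points with drug therapy".

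**The concern.** A before-after test asks whether an arm changed. The hypotheses ask whether the arms differ. In a trial whose two arms both receive active treatment, these questions come apart: the app arm can improve markedly because of conventional treatment, the passage of time and regression to the mean, with no contribution from the app.

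A report that followed the named test could therefore show a significant improvement on the app that says nothing about the app. The usual next step, setting a significant result in one arm against a non-significant one in the other, is not a valid test of a difference. It becomes less reliable when the arms differ in size, because the larger arm reaches significance more easily for the same change.

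**Working it through.** **Inputs from the protocol.** Target 300, loss up to 20%, so 300 × 0.8 = 240 evaluable. Trial design gives 2:1 allocation (160/80), while Sample size also gives 150 per group (120/120 after loss), so both splits are used. α = 0.05, taken as two-sided because sidedness is not stated. Cited PEDT falls: at least 6-7 points with drug therapy, at least 2-3 with psychological or behavioural therapy.

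**The plan's own figure.** The 300 can be neither reproduced nor refuted, because no SD and no between-group difference are given. If the cited 2-3 points are read as the between-group difference (an assumption), the SD that 240 evaluable patients imply at 80% power is

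SD = d / [(1.96 + 0.84) × √(1/n₁ + 1/n₂)]

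- 120/120: 5.5 (d = 2) to 8.3 (d = 3)
- 160/80: 5.2 (d = 2) to 7.8 (d = 3)

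I therefore use an assumed SD of change of 3, 5 and 8.

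**Within-arm test, no app effect.** z = fall / (SD/√n); approximate power = Φ(z − 1.96).

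- Fall 6, SD 8, the least favourable case: z = 6/(8/√160) = 9.5; 6/(8/√120) = 8.2; 6/(8/√80) = 6.7. Power is about 100% in every arm, and z is larger at SD 3 and 5.
- Fall 2, SD 8: z = 3.16 (n = 160), 2.74 (n = 120), 2.24 (n = 80). Power is about 89%, 78% and 61%.

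**Simulation with the kind of test the protocol names.** 1,000 trials per scenario, the same mean fall in both arms, change drawn as a rounded normal variable. Wilcoxon signed-rank within each arm; Mann-Whitney on change between arms.

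| Common fall | SD | Split (app/control) | App arm significant | Only app arm significant | Between-group test significant |
|---|---|---|---|---|---|
| 6 | 3, 5, 8 | both | 100% | 0% | 4.1-4.9% |
| 3 | 8 | 160/80 | 99.5% | 9.1% | 4.9% |
| 3 | 8 | 120/120 | 97.9% | 2.4% | 5.7% |
| 2 | 3 | both | 100% | 0% | 5.0-6.2% |
| 2 | 5 | 160/80 | 99.8% | 6.7% | 4.9% |
| 2 | 5 | 120/120 | 99.4% | 1.2% | 4.4% |
| 2 | 8 | 160/80 | 86.3% | 39.2% | 4.3% |
| 2 | 8 | 120/120 | 75.7% | 18.9% | 5.6% |

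The Monte Carlo standard error near 5% is √(0.05 × 0.95/1000) = 0.7 percentage points, so the last column is consistent with 5%.

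**Reading the table.** Under a null app effect, the named test is significant in most or all trials. The between-group test keeps its nominal error rate on the same data. In the 2-point, SD 8 case, contrasting the two within-arm results would wrongly favour the app in 39% of null trials at 160/80 and 19% at 120/120.

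**Is the right comparison feasible?** Yes, over much of the range. An unadjusted between-group comparison of a 2-point difference at 160/80 has power 99.8%, 83% and 45% at SD 3, 5 and 8. At 120/120 it is 99.9%, 87% and 49%.

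**The case against.** The strongest defence is that a separate SAP may name the comparative model, that the protocol never calls the within-group test primary or sole, and that its hypotheses and outcomes are plainly comparative. The wording may also be a loose rendering of a comparison of changes across groups. That defence would answer a complaint about missing detail. It does not answer this one, because the protocol does name an efficacy test, and the test as worded does not fit its hypotheses. A SAP that follows it inherits the mismatch, and one that departs from it contradicts the protocol.

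Some stronger readings are tempting, and the documents do not support them:

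- A reader might infer that the app arm is certain to show significance whatever the app does. That is near-certain only under the 6-7 point fall cited for drug therapy. Group therapy also lists traditional Chinese medicine and instrument therapy, for which no fall is given. With a 1-point common fall and SD 8, the app-arm test is significant in only about 25% to 35% of null trials.
- A reader might infer that the effect can never be estimated. Group means and SDs will be reported, so a crude difference can be computed. What is missing is a planned estimate with an interval and a test.
- A reader might think that the named test cannot suit a score. The sentence also offers a non-parametric test, and a paired one is reasonable for change in a 0-20 score.
- A reader might take week 8 as the natural primary time point. The protocol makes mean PEDT within 8 weeks primary and lists PEDT at weeks 4 and 8 as secondary, so that choice would alter the primary outcome.

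Testing baseline balance is a matter of preference. It does not bias the effect estimate and is not part of this point.

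**Conclusion.** The point stands, and the text should be changed before any comparative analysis. The one efficacy test in the protocol is within-arm and tests neither Hypothesis 1a nor Hypothesis 2a. The arms are formally compared only at baseline.

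Under the cited drug-therapy fall, a significant app-arm result is close to certain with no app effect. Under a 2-point common fall it remains more likely than not throughout the range examined. The percentages rest on the assumed SDs, roughly normal changes, 240 evaluable patients and two-sided 0.05. The mismatch between test and hypothesis rests on none of these, and it is the same under either allocation. The trial's labelling as exploratory does not remove it, because the stated hypotheses are comparative.

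**What to change.** Replace the before-after sentence in Statistical methods with text along these lines:

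*The primary analysis is the between-group difference in mean PEDT within 8 weeks, estimated from a repeated-measures model over weeks 4 and 8 adjusted for baseline PEDT, and reported with its 95% confidence interval and p-value. PEDT, IELT and FSDS-R-PE at weeks 4 and 8 are compared between groups as secondary outcomes. Changes within each group are described only.*

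The sponsor should confirm that averaging over weeks 4 and 8 is what the primary outcome means. Any SAP should carry the same wording.

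Adjusting for centre, analysing IELT on the log scale and dropping the baseline significance tests are optional.

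The cost is a wording amendment. The baseline, week-4 and week-8 data are already scheduled under Data processing and storage, and the named software can fit the model. No visit, measurement or patient is added.

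### The only outcome test the protocol states is a before-after test within each arm, which on its natural reading cannot answer the between-group Hypotheses 1a and 2a

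*Protocol*

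**What the plan says.** The Objectives and Outcomes section sets two hypotheses, both contrasts between arms. Hypothesis 1a reads "a significant difference in the mean scores of the premature ejaculation diagnostic tool (PEDT) is expected between the two groups within 8 weeks". Hypothesis 2a says that differences in PEDT, IELT and FSDS-R-PE "are expected between the two groups at 4 and 8 weeks". The Trial design section describes a randomised, controlled, parallel-group trial.

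The Statistical methods section contains these statements on inference and group data:

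- Shapiro-Wilk, to check normality.
- Pearson correlation, variables not named: "Pearson correlation analysis will be used to evaluate the correlation, and P<0.05 will be considered statistically significant".
- Description of the groups: "Metric data of different groups will be described statistically using mean, standard deviation, median, minimum value, and maximum value".
- The outcome test: "We will use exact probability calculation or non-parametric test to analyze the changes before and after intervention in each group".
- Baseline balance: "The balance analysis of baseline values will be compared using analysis of variance or exact probability calculation for demographic data and other baseline indicators".

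On treatment, the Group therapy section says "Both patient groups received conventional treatments" and lists several types. The Sample size section cites PEDT falls of at least 2-3 points with psychological or behavioural therapy and at least 6-7 points with drug therapy.

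**The concern.** A within-arm test has the null hypothesis that patients in that arm did not change. Hypotheses 1a and 2a need the null that the two arms do not differ. Both arms receive active background treatment, so the first null can be false in both arms while the second is true. Two significant before-after results would then say nothing about the app, yet they are the only outcome P values the section provides for.

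The randomised comparison is what this trial is built to deliver. If the section were followed as written, Hypothesis 1a, which concerns the primary outcome, would be left without a test. A statistical analysis plan that followed the sentence would inherit the problem, and one that departed from it would contradict the protocol. The sentence therefore needs correcting even if a separate plan exists.

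**Working it through.** **Step 1. Match hypotheses to tests.**

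| Question | Contrast needed | What Statistical methods provides |
|---|---|---|
| Hypothesis 1a: PEDT within 8 weeks | Between arms | Description by group; before-after test in each group |
| Hypothesis 2a: PEDT, IELT, FSDS-R-PE at weeks 4 and 8 | Between arms | The same |
| Baseline balance | Between arms | Analysis of variance or exact test |
| Correlation of unnamed variables | None | Pearson |

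Arms are tested against each other only at baseline. This mismatch needs no calculation.

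**Step 2. Inputs for the size of the problem.**

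- From the protocol: 300 patients, at most 20% loss, so 300 × 0.8 = 240 evaluable. The 2:1 ratio gives 160/80. The Sample size section also says 150 per group, which gives 120/120. Both are shown.
- From the protocol: a 6-point fall (lower end of the drug figure) for the control arm, and a 2-point addition by the app (lower end of the psychological or behavioural figure).
- Assumed: SD of the PEDT change 3, 4 or 5, because the protocol gives none; normally distributed changes; two-sided 0.05; Wilcoxon signed-rank as the within-arm test, because the protocol names no specific one.

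The protocol gives no planned difference and no SD, so it has no power figure of its own to reproduce.

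**Step 3. Within-arm test, approximate.** Signal = fall / (SD/√n). The weakest case is the control arm with n = 80 and SD 5: 6 / (5/√80) = 6 / 0.559 = 10.7, against a critical value of 1.96. The app arm (n = 160) gives 6 / (5/√160) = 15.2 even if the app adds nothing. Both arms are significant almost with certainty.

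**Step 4. Between-arm test.** SE = SD × √(1/n₁ + 1/n₂); power ≈ Φ(2/SE − 1.96) for a 2-point app effect.

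| SD | SE, 160/80 | Power, 160/80 | SE, 120/120 | Power, 120/120 |
|---|---|---|---|---|
| 3 | 0.411 | 99.8% | 0.387 | 99.9% |
| 4 | 0.548 | 95.5% | 0.516 | 97.2% |
| 5 | 0.685 | 83.2% | 0.645 | 87.3% |

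**Step 5. Simulation** (1,500 trials per setting, Wilcoxon within arms, t-test between arms; ranges run over SD 3 to 5).

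| Control fall | App adds | Split | Both arms significant | Between-arm test rejects |
|---|---|---|---|---|
| 6 | 0 | 160/80 | 100% | 4-6% |
| 6 | 2 | 160/80 | 100% | 83-99.9% |
| 6 | 0 | 120/120 | 100% | 4-5% |
| 6 | 2 | 120/120 | 100% | 87-99.9% |

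Using a Mann-Whitney test between arms at 160/80 (1,000 trials, SD 3 and 5) gives 3-5% and 79-99%, so the choice of between-arm test matters little.

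**Step 6. Sensitivity to the control fall** (160/80).

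- Fall of 2 points: both arms are significant in 93-100% of trials with no app effect and in 94-100% with a 2-point effect.
- Fall of 0: the pattern of app arm significant and control arm not occurs in 2-3% of trials with no app effect and in about 97-98% with a 2-point effect. Here the within-arm pattern does follow the app.

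**The case against.** The best defence is that this is an omission rather than an error. The section never calls the before-after test primary, never ties it to a hypothesis and never says it is the only test. The hypotheses and design fix the two-group comparison, and a protocol may leave the name of the test to the statistical analysis plan. That would be a full answer if the protocol were silent. It is not: it states an outcome test, and on its natural reading that test addresses the wrong contrast. What stands is that one cannot conclude that the sponsor intends to abandon the randomised comparison, only that the stated analysis does not contain it.

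A second defence is that the wording is loose. The section also speaks of the balance of each group when it means a comparison across arms, so the outcome sentence might mean changes compared between arms. That is possible, though the within-arm reading is the natural one. If a comparison was meant, the same rewording is needed.

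Two stronger readings are tempting and are not supported:

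- A reader might infer that the stated test always gives the same answer whether or not the app works. That holds only if the control arm improves; Step 6 shows that it fails if the control arm does not change. The 6-7 point figure is for drug therapy, whereas conventional treatment here also includes traditional Chinese medicine and instrument therapy, so the protocol does not credit that fall to every control patient.
- A reader might infer that an inert app is likely to be declared effective because the larger arm alone reaches significance. That needs a common fall smaller than any figure the protocol cites. At a 2-point fall with no app effect, the app-only pattern occurs in 0-7% of trials at 160/80 and about 1% or less at 120/120. Any advantage to the app arm also rests on the 2:1 split, which the 150 per group in the Sample size section contradicts.

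**Conclusion.** The point holds in limited form. Both hypotheses concern differences between randomised arms, and the only outcome test stated is a before-after test in each arm, which cannot answer them. This rests on the text alone.

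The size of the consequence is conditional. If the control arm falls by 6 points, the within-arm results are the same (both significant, 100% of trials) with no app effect and with a 2-point effect, while a between-group test separates the two cases at about 5% against about 83-100%. The figures are similar at 120/120. They rest on an assumed SD of change of 3 to 5, normal changes, 240 evaluable patients and an improving control arm. The protocol's own treatment figures make that improvement likely but do not guarantee it. Because the primary hypothesis is affected and the repair is cheap, the wording should be corrected before analysis.

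**What to change.** Replace the before-after sentence in Statistical methods with:

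> The primary analysis compares PEDT between the two randomised groups over the period named in Hypothesis 1a (within 8 weeks), reporting the between-group difference with its 95% confidence interval and a two-sided P value at the 0.05 level. PEDT, IELT and FSDS-R-PE at weeks 4 and 8 are compared between groups in the same way as secondary analyses. Within-group changes are supportive and are not used to conclude efficacy.

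The sponsor must also state which PEDT summary the phrase within 8 weeks means, for example the week-8 value or the mean of weeks 4 and 8. Without that the primary comparison cannot be carried out as written.

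Removing the Pearson correlation is optional and not part of this defect.

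Cost: one paragraph in the protocol, with matching wording in any statistical analysis plan. No new data, visits or patients.
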